### Outcome measures

2.7

#### Primary outcome

2.7.1

Participants will self-report symptom intensity scores before the first treatment and after weekly treatments during the trial. The participants are required to self assess the severity of their four nasal symptoms (sneezing, watery rhinorrhea, nasal congestion, and nasal itching) and 4 non-nasal symptoms (ocular itching, watering, redness, itching of the ears, and/or palate) by using a 10-cm Visual Analogue Scale (VAS) (17) that ranges from “no symptoms” to “worst symptoms ever”. Scores will be assessed at baseline (before treatment initiation) and after each week of treatment.

#### Secondary outcome

2.7.2

1.The participants self assess the four nasal symptoms (nasal obstruction, rhinorrhea, sneezing, and itching) involved in assigning the total nasal symptom score (TNSS) (18). The symptoms were graded on a five-point scale (where 0 indicates no symptoms, a score of 1 for mild symptoms that are easily tolerated, 2 for awareness of symptoms which are bothersome but tolerable and 3 is reserved for severe symptoms that are hard to tolerate and interfere with daily activity). Score will be calculated before the treatment and after everytime treatment.2.The efficacy was evaluated according to the improvement of TNSS score

Efficacy index (%) = (TNSS total score before treatment-total score after treatment)/ total score before treatment ×100% (19).

Obvious effect: the nasal symptoms were significantly improved after treatment, and the curative effect was >76%;

Effective: Nasal symptoms improved after treatment, 26%≤curative effect ≤76%;

Ineffective: Nasal symptoms did not significantly reduce after treatment, and the curative effect was <26%.
3.Onset time of effectAfter the treatment begin, the number of treatments will be recorded when the Efficacy index reaches 26%.
4.Quality of life score of AR patients:The participants self assess symtoms by using the Rhinitis Quality of Life Questionnaire (RQLQ) (20), which has 28 questions in 7 items ranked from 0 to 6.

Score will be calculated before the treatment and after weekly treatment.
5.Safety evaluationAdverse events (AEs) will be recorded on the Case Report Form (CRF), including the initial symptom presentation date, recovery timeline, intensity grading, treatment-associated occurrences, and final outcome status (resolution or persistence). AEs associated with acupuncture include needle stagnation, needle fainting, hematoma, or other discomfort. In the event of AEs, the research team will administer necessary medical care and provide corresponding reimbursement, while simultaneously notifying the Data and Safety Monitoring Board for documentation and review.

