### Participant and consumer involvement

2.2

Inclusion criteria includes a diagnosis of perennial allergic rhinitis (14), between the age of 18 and 60. All participants will sign consent documents before participation. Exclusion criteria includes: Severe comorbidities (e.g.,uncontrolled hypertension, diabetes, malignancies, organ dysfunction).Nasal abnormalities, sinusitis, asthma, or prior nasal surgery. Recent use of corticosteroids/Antihistamines (1 month) or immunotherapy (1 year). Prior acupuncture experience or pregnancy/lactation. Withdrawal Criteria includes using rescue medicine 3 times/week,rescue medicine-related Adverse Event ≥Grade 2 (CTCAE v5.0); experiencing severe complications or other serious illnesses and is unable to continue cooperation. Data were analyzed by intention-to-treat (ITT).

All participants provided informed consent and could withdraw anytime. Data were used solely for research purposes.

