#### Randomization

2.8.2

The randomization sequence was generated by an independent statistician using SAS version 9.4 (SAS Institute, Cary, NC, USA) with a block randomization algorithm (block sizes of 4 and 6) to ensure balanced allocation between groups. Participants were stratified by disease severity into two strata (mild vs. moderate-to-severe) according to the ARIA guidelines (2016 revision) (14), Within each stratum, participants were randomized 1:1 to either the treatment or control group. The randomization sequence was concealed in opaque, sequentially numbered envelopes, which were opened only after baseline data collection to ensure allocation concealment (21). To ensure baseline comparability between groups, we monitored the distribution of key variables, including age (18–40 vs. 41–60 years), sex, disease duration (≤5 vs. >5 years), and baseline VAS scores. Any significant imbalances detected during the study were adjusted for in the final analysis using appropriate statistical methods.

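### The Efficacy index divides by one pre-treatment TNSS with no minimum entry score, so its categories and the onset time mean different things at different baselines; make baseline-adjusted TNSS in points the main TNSS comparison

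*Protocol article*

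**What the plan says.** All references are to the protocol article.

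- **Formula (2.7.2, item 2).** The index is ("TNSS total score before treatment-total score after treatment)/ total score before treatment ×100"%). *Obvious effect* is defined by "the curative effect was >76"%, *Effective* by "26%≤curative effect ≤76"%, and *Ineffective* is anything below 26%.
- **Timing (2.7.2, item 1).** "Score will be calculated before the treatment and after everytime treatment". Table 1 marks TNSS once at enrolment and then after each treatment. There are 12 sessions (2.5).
- **Scale (2.7.2, item 1).** Four nasal symptoms are scored. "The symptoms were graded on a five-point scale (where 0 indicates no symptoms", and then "a score of 1 for mild symptoms that are easily tolerated", up to 3 for severe symptoms. Only grades 0 to 3 are described.
- **Onset (2.7.2, item 3).** Onset is the number of treatments at which the same index reaches 26%.
- **Entry (2.2).** "Inclusion criteria includes a diagnosis of perennial allergic rhinitis (14), between the age of 18 and 60". The exclusions that follow set no minimum TNSS or VAS.
- **Strata (2.8.2).** "Participants were stratified by disease severity into two strata (mild vs. moderate-to-severe").
- **Analysis (2.8.4).** Two-sample and categorical tests, with generalized estimating equations or mixed models for time-by-treatment interaction and rescue medication as a covariate.

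**The concern.** A percentage change in a small whole-number score is coarse, and most so where the denominator is smallest. The trial admits mild patients without a floor, so small denominators are possible by design. Fixed percentage cut-offs then turn into different numbers of points for different patients.

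Two secondary outcomes depend on this one formula: the three-level response and the onset time. If a participant's category depends heavily on where they started, a response rate is hard to read as clinical benefit. Onset is a first crossing over as many as 12 readings, so it is also exposed to ordinary fluctuation at low baselines. That matters because the Discussion hopes the time-effect relationship will help to optimize treatment frequency and duration.

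**Working it through.** The documents state no figure that can be reproduced on this point. The check applies their own formula to every possible baseline.

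**Inputs.** Index = (B − A)/B × 100%, where B is TNSS before treatment and A is TNSS after a session. The cut-offs are at least 26% and above 76% (2.7.2). Four items at 0–3 give a total of 0–12.

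**Step 1: exact enumeration.** For each B, find the smallest whole number k with k/B ≥ 0.26, and the smallest with k/B > 0.76.

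| Baseline B | A 1-point fall gives | Points to reach 26% | Points for *Obvious effect* |
|---|---|---|---|
| 0 | undefined | – | – |
| 1 | 100% | 1 | 1 |
| 2 | 50.0% | 1 | 2 |
| 3 | 33.3% | 1 | 3 |
| 4 | 25.0% | 2 | 4 |
| 5 | 20.0% | 2 | 4 |
| 6 | 16.7% | 2 | 5 |
| 7 | 14.3% | 2 | 6 |
| 8 | 12.5% | 3 | 7 |
| 9 | 11.1% | 3 | 7 |
| 10 | 10.0% | 3 | 8 |
| 11 | 9.1% | 3 | 9 |
| 12 | 8.3% | 4 | 10 |

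- At B = 1 a 1-point fall is already *Obvious effect*, so *Effective* cannot occur.
- At B = 1 to 4, *Obvious effect* requires complete clearance.
- From 3 to 2: 1/3 = 33.3%, *Effective*. From 8 to 6: 2/8 = 25.0%, *Ineffective*. The smaller improvement gets the better category.
- Item 1 calls the scale five-point. If items ran 0–4, the total would be 0–16; baselines 13–15 would need 4 points and 16 would need 5. The pattern is the same.

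**Step 2: how much noise alone could do (assumptions, not in the documents).** Take no true change, rounded normal readings, and zero correlation between the baseline and session errors. The chance of reaching 26% at one session, among participants with a baseline above 0, is:

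| Session SD (assumed) | True TNSS 3 | 5 | 7 | 9 |
|---|---|---|---|---|
| 1.5 | 34% | 24% | 16% | 11% |
| 1.0 | 26% | 15% | 7% | 4% |
| 0.75 | 21% | 9% | 2% | 1% |

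Correlated errors lower these rates. At true TNSS 3 and SD 1.0, the rate is 20% with correlation 0.5 and 13% with correlation 0.8. The chance that a participant with true TNSS 3 reads 0 at baseline is 4.8%, 0.6% and 0.04% at SDs of 1.5, 1.0 and 0.75.

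**Step 3: onset (a second assumed model).** Fix the baseline, assume no true change, and let each item move up or down 1 point with probability 5% to 20% each way, independently at 12 visits. The chance of ever reaching 26% is about 80%–98% at baseline 3, 14%–76% at baseline 4 and 0.6%–22% at baseline 8.

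The absolute rates in steps 2 and 3 move widely with the assumptions. The gradient by baseline is present in every setting tabulated.

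**The case against.** The strongest reply has five parts.

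1. **Any percentage-change measure depends on baseline, and this definition comes from a cited source.** True. But the cut-offs are fixed here for a population with no entry floor, and the whole-number arithmetic follows directly from that.
2. **TNSS in points is already a secondary outcome, and mixed models are planned.** This stands in large part, and it makes the remedy cheap. What the article does not do is rank points above the index. Its analysis section names neither baseline TNSS nor the severity stratum as a model term.
3. **A baseline of 0 is remote, and its handling belongs in the analysis plan.** Largely right. Patients must have the diagnosis and no antihistamines or corticosteroids in the previous month. The absence of a zero-baseline rule is not in itself a fault of a condensed article. The ranking problem at baselines 1–12 does not depend on it.
4. **There is no bias between arms.** This stands. Allocation is 1:1 in blocks within severity strata, so low baselines should be roughly balanced. A reader might infer that the index favours one arm; the documents do not support that.
5. **Noise rates rest on assumed inputs.** This stands too. No single false-response percentage can be quoted for this trial.

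A reader might also infer that a 1-point fall makes any mild patient a responder. It does so only at baseline 1–3. A patient with four mild symptoms has TNSS 4, and a 1-point fall is then 25.0%, *Ineffective*. The article does not map the mild stratum to a TNSS range, so the share at 0–3 is unknown.

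**Conclusion.** The concern holds in a limited form. As written, the points needed to reach 26% rise from 1 to 4 across baselines 1 to 12. Smaller improvements can outrank larger ones, the onset time inherits the same threshold, and the index has no value at baseline 0. These results are exact, given the formula, the cut-offs and whole-number scoring.

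The practical size depends on how many participants start at TNSS 0–3 and on session-to-session SD and correlation. The documents give none of these, so only ranges can be shown. The damage is to precision and interpretability of secondary outcomes. The primary VAS outcome and the sample size, which rests on VAS, are untouched. The change is worth making because it is nearly free.

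**What to change.** - In 2.7.2 and 2.8.4, name TNSS in points as the main TNSS comparison. Estimate it from a model adjusted for baseline TNSS and the randomization severity stratum; the mixed model already planned, run over the sessions, would serve.
- Label the Efficacy index categories and the index-based onset time as supportive.
- Keep all randomized participants in the points analysis, in line with the stated intention-to-treat principle.
- State in advance, identically for both arms, that the index is not computed at baseline 0, and report how many participants this affects.
- Do not add a minimum fall of 2 points or exclude baseline 1. From baseline 4 upward the cut-off already needs at least 2 points, so a floor changes nothing there. At baseline 2 it would demand complete clearance. Excluding randomized participants sits poorly with intention-to-treat.

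Cost: wording and analysis code, with no new data. Downside: the index carries less weight than in the definition the article cites.

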**Methods:**

This clinical trial features a stratified randomization scheme with 1:1 allocation, single-blind assessment, and a total sample size of 84 participants. After screening for inclusion, qualified subjects with perennial allergic rhinitis will be randomly allocated to treatment group(accepting acupuncture, *n* = 42) or control group (accepting sham acupuncture, *n* = 42). The intervention will last over a 4-week period. The main efficacy outcome is the change in main symptom severity assessed by the Visual Analogue Scale (VAS) after each week of treatment. Secondary outcomes include the Total Nasal Symptom Score (TNSS), Efficacy Index (%) after each treatment session, time to onset of effect, Rhinitis Quality of Life Questionnaire (RQLQ) scores after each week of treatment, and the additional use rate of anti-allergic medications.

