### Interventions

2.5

Both groups will undergo 12 sessions with eye masks. Participants in the treatment group will undergo acupuncture by 0.25 × 40 mm disposable needles (Guizhou Andy Pharmaceutical Equipment Co., Ltd., Guizhou, China). Following skin sterilization, aseptic adhesive pads will be positioned GB20 on both sides, and acupuncture needles are inserted through the pads to a depth of roughly 10–15 mm, following the direction of the nasal tip. Upon needle placement, gentle and uniform twirling at a frequency of approximately 60 rotations per minute, with a rotation angle of approximately 180°-360° (STRICTA 2010 guidelines) are performed to achieve *de qi* (a characteristic sensations encompassing soreness, numbness,fullness, and a heavy feeling), which is regarded as a crucial factor for therapeutic effectiveness in acupuncture. The needles are then retained at GB20. Subsequently, aseptic adhesive pads are placed on bilateral LI20, ST7, LI4, and GV29. Acupuncture needles are inserted through the pads to depths of 10–20 mm (10 mm for LI20 and GV29; 20 mm for ST7 and LI4), following the direction of the nasal tip. After insertion, twirling manipulations are performed on all needles to achieve *de qi*. All needles are retained for 20 minutes.

Participants in the control group will receive sham acupuncture using pragmatic placebo needles (0.25 mm in diameter × 30 mm; “Andy” brand disposable sterile flat-head needles; Guizhou Andy Pharmaceutical Equipment Co., Ltd.) at non-acupoint locations (Figure 2 and Table 2). The procedures and treatment settings in the control group are identical to those in the treatment group,with the exception that neither skin penetration nor needle manipulation to elicit *de qi* is administered.

Both procedures follow Liu's research (15) and SHARE guidelines (16).

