#### Analytical methods

2.8.4

Statistical analyses will be conducted utilizing the SAS software package, with statistical significance defined as *P* < 0.05. For continuous data following normal distribution, results will be reported as mean ± SD; non-normally distributed data will be presented as median (IQR). Continuous variables will be assessed by the *t*-test or Mann–Whitney *U*-test. Categorical data will be summarized as frequencies (percentages) and evaluated through *χ*^2^ tests or Fisher's exact tests. Additionally, time-by-treatment interactions will be analyzed employing generalized estimating equations or mixed-effects models. All statistical tests will use a 95% confidence level, considering results significant when *P* values are below 0.05.Rescue medication use will be incorporated as a covariate. To ensure robustness, we will conduct sensitivity analyses. Besides, we wil also do exploratory subgroup analysis stratified by whever they use rescue medication or not.

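### Onset time has no value for participants who never reach the 26% threshold, no rule covers them, and the listed tests on recorded values would in effect compare only those who did

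*Protocol article*

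**What the plan says.** The abstract lists "time to onset of effect" among the secondary outcomes. Section 2.7.2, item 3, makes it operational: after treatment begins, "the number of treatments will be recorded when the Efficacy index reaches 26" per cent. Item 2 of the same section calculates the Efficacy index from the TNSS total before and after treatment, and has a lowest class: "Ineffective: Nasal symptoms did not significantly reduce after treatment, and the curative effect was <26" per cent.

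Section 2.5 fixes the number of opportunities to cross the threshold: "Both groups will undergo 12 sessions with eye masks". Table 1 schedules TNSS and the Efficacy index after every session.

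On analysis, section 2.8.4 says "Continuous variables will be assessed by the *t*-test or Mann–Whitney *U*-test". It adds chi-square or Fisher tests for categorical data, and states that "time-by-treatment interactions will be analyzed employing generalized estimating equations or mixed-effects models". No time-to-event method is named. Section 2.2 states "Data were analyzed by intention-to-treat (ITT") and also allows participants to leave before onset: "Withdrawal Criteria includes using rescue medicine 3 times/week". Section 2.8.1 allows for 20% dropout.

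**The concern.** The recorded quantity exists only for participants who cross 26%. For anyone still below 26% after session 12, all that is known is that onset would have come later, if at all. For anyone who leaves earlier without crossing, onset is unknown beyond the last visit. These are right-censored observations, and the article neither scores them nor names a method that accommodates them.

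If the listed t-test or Mann–Whitney is run on the numbers that exist, the comparison is between those who responded in one arm and those who responded in the other. Membership of that subset is itself affected by treatment, so randomisation no longer protects the comparison. The test then asks how fast responders responded and ignores how many there were. If acupuncture brings more people to onset at the same speed, the test sees nothing. If it also brings slower responders across the threshold, the result can point towards sham. The abstract's conclusion names time-effect relationships among the trial's aims, and onset time is one of the outcomes that bears on them.

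**Working it through.** **1. The plan's own figure.** The article gives no expected onset time, reach or power for this outcome, so there is nothing to reproduce. The sample size in section 2.8.1 concerns the VAS outcome and is not touched by this point.

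**2. Inputs.** From the article: 42 per arm (abstract), at most 12 sessions (section 2.5), threshold 26% (section 2.7.2), two-sided 5% significance (section 2.8.4). Assumed, because the article does not give them: the share q of an arm that can ever reach 26%, and the per-session chance h of crossing among those who can. The onset session is taken as geometric, and crossings after session 12 are not recorded. Early withdrawal is not simulated.

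**3. Who is left in a reachers-only test.** Share with a recorded value = q × [1 − (1 − h)^12]. With h = 0.35, 0.65^12 = 0.0057, so the bracket is 0.994.
- q = 0.80: 42 × 0.80 × 0.994 = 33.4 participants.
- q = 0.50: 42 × 0.50 × 0.994 = 20.9 participants.

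About 54 of 84 enter the test. With equal h, onset among reachers has the same distribution in both arms, so a reachers-only test should reject at about its nominal 5% however far apart 80% and 50% are.

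**4. Rejection rates by simulation** (thousands of trials per row; rates vary by a point or so between runs):

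| Assumed reach (acupuncture v sham) | Assumed per-session chance | Mann–Whitney, reachers only | Mann–Whitney, all 84, non-reachers ranked last | Log-rank, non-reachers censored at session 12 |
|---|---|---|---|---|
| 80% v 50% | 0.35 v 0.35 | about 4–5% | about 70% | about 80% |
| 90% v 80% | 0.35 v 0.35 | about 4–5% | about 11–13% | about 20% |
| 95% v 95% | 0.52 v 0.30 | about 74% | about 71% | about 55% |
| 90% v 90% | 0.35 v 0.35 | about 5% | about 5% | about 5% |

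The last row has no difference between arms and shows that keeping everyone does not inflate the error rate.

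**5. Reversal.** Mean onset among reachers = 1/h − 12(1 − h)^12 / [1 − (1 − h)^12]. Take reach 90% v 50% with h = 0.25 v 0.40, so that sham's fewer reachers are quicker.
- Acupuncture: 0.75^12 = 0.0317; 4 − 12 × 0.0317/0.9683 = 3.6 sessions, from 42 × 0.90 × 0.968 = 36.6 participants.
- Sham: 0.60^12 = 0.0022; 2.5 − 12 × 0.0022/0.9978 = 2.5 sessions, from 42 × 0.50 × 0.998 = 21.0 participants.

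The reachers-only means favour sham by about 1.1 sessions although some 16 more acupuncture participants reach onset. The reachers-only Mann–Whitney rejects in about 37% of such trials.

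**The case against.** The strongest objection is that this is detail for an analysis plan that is not shown. That would hold if the article were silent on analysis. It is not: it fixes the endpoint and names the test families, and the two do not fit without a further rule.

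Several limits on the point stand:
- A reader might infer that the plan excludes non-reachers. No sentence says so, and the intention-to-treat statement points the other way. Exclusion is what follows from running the listed tests on the recorded values, because the others have none.
- Section 2.8.4 does not assign a test to onset time by name. Mann–Whitney, which is listed, copes well if non-reachers are ranked last. A t-test would need an invented number.
- A reader might take the lowest Efficacy index class as proof that the plan expects people never to reach 26%. The index is calculated after each session, so a low class at one session does not show failure at all 12. Non-reachers are plausible, but their number is unknown. The Discussion cites an immediate effective rate of 52.1% after the first acupuncture session, and there are further sessions in which to cross.
- A reader might infer that the trial would miss a large benefit. A difference in reach should also show in the Efficacy index classes under the listed chi-square or Fisher tests, and in the repeated TNSS.
- Censoring is not neutral for everyone. Withdrawal for frequent rescue use is driven by symptoms, so censoring those participants at their last TNSS may be informative.

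**Conclusion.** The point holds as a misfit between a stated secondary endpoint and the stated tests. Participants without onset have no value and no rule, and the listed tests on recorded numbers would compare an outcome-selected subset, at odds with intention-to-treat.

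The harm depends on how far reach differs between arms, which the documents do not say. Under the assumed inputs, a reachers-only test stays at about 4–5% when only reach differs, whether the difference is large (80% v 50%) or modest (90% v 80%). An analysis of all participants then rejects in about 70–80% and 11–20% of trials respectively. It would be wrong to read the first case as typical, or to conclude that log-rank is always better. With equal 95% reach and different speed, reachers-only and ranked-last Mann–Whitney give about 74% and 71% against 55% for log-rank. The case for keeping everyone rests on preserving the randomised comparison, not on power in every scenario.

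The importance is moderate: one secondary outcome, with no effect on the primary analysis or the sample size.

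**What to change.** Define onset as the first session at which the Efficacy index is at least 26%, calculated against the TNSS taken before the first treatment. Analyse all randomised participants, with those who complete without crossing censored at session 12. Present cumulative onset by session and arm. Compare arms with a log-rank test stratified by the severity strata used at randomisation, or with a discrete-time model, which can also carry covariates. To stay within the listed tests, use Mann–Whitney on everyone with non-reachers ranked last. Choose one of these as the main analysis before the data are seen, since none is best in every scenario.

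State how early leavers are handled. In the main or a sensitivity analysis, count participants withdrawn for rescue use or lack of effect as non-reachers rather than censoring them at their last TNSS.

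The cost is a few sentences of wording and slightly more analysis work. TNSS is already scheduled before treatment and after every session, so no visit or measurement is added.
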